**Eligibility criteria**

**Inclusion criteria:** single pregnancy (from 22/0 to 26/0 weeks of gestation), with classic PPROM with oligo/anhydramnion between 20/0 and 26/0 weeks of gestation. From the beginning of 22/0 weeks of gestation, the PPROM duration must be lower as of five days till randomization. The patients will receive RDS prophylaxis (respiratory distress syndrome) before randomization. The vertical deepest amniotic fluid depot must be <2 cm, and the amniotic fluid Index < 3. The PPROM will be confirmed by positive testing of the placental alpha microglobulin-1 and the amniotic fluid that is clearly lost (Figure 2, flow diagram).

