**Sample size and Statistic**

The sample-size calculation was based on the primary outcome (binary yes/no) survival without major morbidities (severe bronchopulmonary dysplasia (BPD), and/or grade 3 or 4 intraventricular hemorrhage (IVH 3–4), and/or necrotizing enterocolitis (NEC) and/or cystic periventricular leukomalacia (cPVL)).

The intervention is expected to prolong the gestation by around two weeks, resulting in an increase of the one-year survival rate without major morbidities after 27 gestational weeks of 67% (hazard = 0.0334). Based on Chen et al. (2016), the one-year survival rate without major morbidities after 25 weeks of gestation is around 36% (hazard = 0.0851) [23]. To be more conservative, the sample-size calculation was based on a hazard = 0.035 for the interventional group. Using a recruiting period of 21 months (four women per month) and an individual follow-up of one year, 34 women are needed in each group for a two-sided log-rank test with 5% significance level, a power of 80% and a loss-to-follow-up rate of 10% per year (hazard = 0.0088). Calculations were performed by PASS software.

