**Assignment of interventions: allocation, concealment mechanism and implementation**

The randomization will be performed by using the randomizer of the center of the clinical studies of the Martin-Luther University Halle-Wittenberg, Germany (computer-generated random numbers). Before the randomization, the inclusion and exclusion criteria of the study will be printed by investigators into the randomizing table online. Matching criteria will be automatically analyzed, and the group of the study and the number will be generated online.

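### The only test the article names is unadjusted, although women enter across four weeks of gestation; gestational age at randomisation should be a prespecified covariate, for a modest gain in power

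*Protocol article*

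**What the plan says.** All references are to the Protocol article.

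- **Entry window.** The Eligibility criteria admit a "single pregnancy (from 22/0 to 26/0 weeks of gestation", and the Abstract gives the same window for randomisation.
- **Test.** Sample size and Statistic bases 34 women per group on "a two-sided log-rank test with 5% significance level". No other test appears. Section 5, Statistical Analysis, says only who will analyse the data; it names no test, model or covariate.
- **Planning rates.** The control rate is that "the one-year survival rate without major morbidities after 25 weeks of gestation is around 36" per cent. The intervention rate is one "after 27 gestational weeks of 67% (hazard = 0.0334" per month). The link between them is that "The intervention is expected to prolong the gestation by around two weeks".
- **Endpoint.** Outcomes defines the primary outcome as binary, one year after delivery. Gestational age at delivery is a secondary outcome.
- **Allocation.** The allocation section refers to "computer-generated random numbers". It names no stratification factor. It mentions matching criteria without defining them; in context this reads as an eligibility check.

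**The concern.** Four weeks is a wide entry window at this stage of pregnancy. Age at delivery equals age at randomisation plus latency. A woman randomised at 26/0 cannot deliver at 23 weeks, whereas one randomised at 22/0 can. For delivery at 23 weeks the article's Discussion cites perinatal mortality of 89.9%. Age at entry should therefore predict the primary outcome.

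With 68 women and no named stratification, an unadjusted comparison gives up some power and leaves any chance imbalance in age uncorrected. If the decision to adjust were taken only after an imbalance was seen, it would be data-driven and open to challenge.

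**Working it through.** **1. Reproducing the stated sample size.** The hazards are monthly: -ln(0.36)/12 = 0.0851 and -ln(0.67)/12 = 0.0334. The article states that "the sample-size calculation was based on a hazard = 0.035 for the interventional group", which gives exp(-12 × 0.035) = 65.7% at one year and a hazard ratio of 0.035/0.0851 = 0.411.

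Schoenfeld events: 4 × (1.96 + 0.842)² / (ln 0.411)² ≈ 40. With 21 months of accrual, follow-up of 12 to 33 months and loss hazard 0.0088, the event probabilities are 0.778 and 0.490 (mean 0.634). That gives 40 / 0.634 / 2 = 31.5 per arm. Freedman (46 events) gives 36.3 and Lachin-Foulkes 34.6, so the stated 34 is reproduced. With follow-up fixed at 12 months the same three methods give 43, 49 and 47. That is a separate matter; it is why power is shown below for both follow-up patterns.

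**2. The gradient in the planning rates.** Log-odds slope = [logit(0.67) - logit(0.36)]/2 = [0.708 - (-0.575)]/2 = 0.64 per week, an odds ratio of 1.90. On the hazard scale it is √(0.0334/0.0851) = 0.626 per week. Both describe gestational age at **delivery**. For age at randomisation they serve here as the strongest gradient considered.

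**3. Chance imbalance.** Assume entry uniform over 22 to 26 weeks (the article gives no distribution). The SD of age is 4/√12 = 1.155 weeks. The SD of the between-arm difference in means is 1.155 × √(2/34) = 0.28 weeks. A difference above 0.5 weeks is |Z| > 0.5/0.28 = 1.785, probability 7.4%. At the full gradient, half a week shifts the log-odds by 0.5 × 0.64 = 0.32.

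**4. Power at 34 per arm, by simulation** (marginal rates 36% and 65.7%, uniform entry).

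Log-rank test against Cox model adjusted for age at randomisation, 4,000 trials per setting:

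| Hazard ratio per week | Fixed 12 months: unadjusted | Fixed 12 months: adjusted | 12–33 months: unadjusted | 12–33 months: adjusted |
|---|---|---|---|---|
| 1.00 | 70.2% | 68.5% | 82.1% | 81.3% |
| 0.89 | 70.1% | 69.2% | not run | not run |
| 0.79 | 70.4% | 71.0% | 81.3% | 82.7% |
| 0.70 | 69.8% | 73.4% | not run | not run |
| 0.626 | 70.8% | 76.6% | 79.8% | 87.0% |

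The change runs from about -2 points (68.5 - 70.2) to +7 (87.0 - 79.8). Type I error at fixed follow-up is 4.9–5.6% unadjusted and 4.6–5.1% adjusted.

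For the binary one-year outcome, logistic likelihood-ratio tests give about 70–71% unadjusted. Adjusted power is 71% at slope 0, 73% at slope 0.4–0.5 and 76% at slope 0.64. Type I error is 5–6% for both.

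**5. How much of the gradient carries over.** Take the delivery slope as 0.64 and add a random latency independent of age at entry, with the intervention adding two weeks (the latency distributions are assumed):

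| Mean latency, control / intervention | Slope on age at randomisation | Unadjusted power | Adjusted power |
|---|---|---|---|
| 1 / 3 weeks | 0.59–0.61 | 68–71% | 74% |
| 2 / 4 weeks | 0.50 | 71% | 74% |
| 3 / 5 weeks | 0.42 | 71% | 73.5% |

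The plausible gain is about 2 to 5 points.

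**The case against.** **The planning figures concern delivery, not entry.** A reader might infer that the plan's own rates show age at randomisation nearly doubling the chance of a good outcome over two weeks (67/36 = 1.86). The documents do not support that. The rates are tied to the expected prolongation, so they describe a post-randomisation variable that the treatment is meant to change. No outcome rate by age at entry is given. This objection stands: the size of the covariate effect is an assumption.

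**Silence is not error.** The log-rank test is named to size the trial, which does not exclude an adjusted primary analysis. Covariates are commonly left to the full protocol or the analysis plan, neither of which is shown, and Data collection and management says that prognostic factors are recorded. This also stands. If the plan already adjusts, the action is only to confirm it. The one test that the article does name can still be improved upon.

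**Adjustment is not free.** If age at entry were not prognostic, Cox adjustment would cost up to about 2 points. The adjusted hazard ratio is also a conditional effect: 0.375 against 0.411 marginal at the strongest gradient. Logistic adjustment costs essentially nothing at slope 0, and standardising to a risk difference restores a marginal effect.

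**Imbalance.** A reader might infer that a material imbalance is likely. At 7.4% for more than half a week it is not, and the unadjusted test keeps its type I error.

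**Conclusion.** The point holds as a modest improvement in method; it does not make the named test invalid. The only test named is unadjusted, entry spans four weeks of gestation, and a baseline value known for every woman is very probably prognostic. Adjusting for it is worth about 2 to 5 points of power under plausible gradients (range about -2 to +7), with no extra women and type I error essentially unchanged.

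The size rests on three assumptions that the documents do not settle: uniform entry over 22 to 26 weeks, marginal one-year rates of 36% and 65.7%, and the share of the at-delivery gradient that carries over to age at entry. Whether a change is needed at all depends on an analysis plan that is not shown.

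**What to change.** Before outcome data are analysed, state in the analysis plan, or confirm that it already states, that the primary analysis of the binary one-year outcome adjusts for gestational age at randomisation as a continuous covariate. A logistic model with the treatment effect standardised to a risk difference would do. State also that gestational age at delivery is never used as a covariate, because it lies on the treatment pathway. Keep the unadjusted comparison as a sensitivity analysis.

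The cost is a few sentences. No new data or additional women are needed, because age at randomisation is already established for eligibility. The small statistical downside, up to about 2 points of power, arises with Cox adjustment if the covariate proves not to be prognostic.

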**Recruitment:**

German gynecologists received flyers for the trial twice (2021 and 2022) in order to achieve adequate participant enrolment to reach the sample size. Additionally, a website for the study, via Google advert (keyword: “Amnion Flush Method”), was created.

**Assignment of interventions: allocation, concealment mechanism and implementation**

The randomization will be performed by using the randomizer of the center of the clinical studies of the Martin-Luther University Halle-Wittenberg, Germany (computer-generated random numbers). Before the randomization, the inclusion and exclusion criteria of the study will be printed by investigators into the randomizing table online. Matching criteria will be automatically analyzed, and the group of the study and the number will be generated online.

**Data collection and management**

The trial is registered with a full description at the German Clinical Trials Register (Deutsches Register Klinischer Studien, DRKS) and at Clinical Trials Register (ClinicalTrial.gov). The study’s protocol is published at the start of the trial.

The Coordination Center for Clinical Trials, University of Halle (Saale), is responsible for data management and archiving. The data will be managed and archived according to existing standards and regulations, in a data format, allowing long-term preservation and future reuse.

The data sheet will be completed when the baby is discharged from the hospital or after death. Any missing data will be reconciled by the chief investigator and trial administrator via contact with the PIs and examination of the hospital’s case notes. The data pack will be returned to the trial co-ordination centers after the baby is discharged or after death.

*P**ost-trial follow-up* is at 6 and 12 months postpartum, when questionnaires are sent to mothers’ home addresses for the assessment of subjective variables, as well as variables pertaining to neonatal medical care for the health/economic evaluation.

**CRF** will include data for recruitment and confirmation of eligibility, informed consent, baseline data, process, data during treatment, primary and secondary outcomes, other outcomes, safety variables, prognostic factors, various questionnaires, as well as data of the pediatric evaluations.

The KKS will receive the copies of pediatric examinations. Neurodevelopmental assessments as well as the check-up of the surviving children will be performed in medical centers by trained pediatric specialists.

**Monitoring**

The coordinating investigator is responsible for implementing and maintaining quality assurance and quality control systems with written SOPs to ensure that the trial is conducted and data are generated, documented and reported in compliance with the protocol, ICH–GCP and the applicable regulatory requirements. Tasks assigned to KKS Halle (see chapter 9, trial supporting facilities) will be fulfilled according to the written SOPs from KKS Halle and the German-wide KKS Network. Data from source documents will be transcribed onto the case report forms (CRFs) by the clinical research staff of each trial site. All source documents will be kept at the trial site, and no information in source documents about the identity of the patients will be disclosed. Pre-trial visits and on-site monitoring will be conducted by trained CRAs from KKS Halle. A total of 3–5 pre-trial visits will be performed to allow for the selection of 3 sites for participation. Based on the pre-trial visit reports, the PI and the steering committee will decide on the participation of the respective trial site. Because of previous on-site selection visits, for initiation of the study centers, conference calls (each site separately) will be considered. Initiation will be supported by .ppt presentations and study materials (investigator’s site file, protocol, informed consent and CRFs) earlier supplied to the sites. On-site monitoring will be performed on a risk-based approach and will be planned by means of regular visits from the beginning to the end of the trial to check the completeness of patient records, the consistency of entries on the CRFs and the adherence to the protocol and to Good Clinical Practice. Initially, the informed consent forms and the adherence to the inclusion and exclusion criteria will be checked. Thereafter, a formal check of captured information for completeness and plausibility will be performed, followed by a check of the correct transfer of data from the source data. Full (100%) source-data verification for the presence of informed consent and adherence to the inclusion/exclusion criteria will be performed. Data used for all primary and safety variables will also be 100% source-data verified. The specific extent of the monitoring and the source-data verification will be specified in the monitoring manual. Each trial site will be monitored once after the first trial participant has been enrolled and treated. The early monitoring shall ensure prompt intervention by the CRA or study center in case of any problems at the trial site, such as major inconsistencies in trial conduction and CRF completion. Another 7 (average, individual number depending on recruiting rate and quality of CRF completion) monitoring visits at each trial site will be conducted during the enrolment period. Every trial site will undergo a close-out visit by the CRA after the last participant at that site has finished the follow-up. The monitor’s access to the trial documents and medical records is ensured by the investigator’s agreement and the cooperation agreement between the sponsor and KKS Halle.

## 5. Statistical Analysis

The collected data will be analyzed by specialists of statistic of the Institute of Medical Epidemiology, Biostatistics and Informatics, Martin-Luther-University Halle-Wittenberg, Germany.

**Adverse event reporting harms**

The Data Safety Monitoring Board (DSMB) will follow the progress of the clinical trial; evaluate the safety and primary efficacy parameters; and will propose to the sponsor whether to continue, modify or stop a trial and provide the funding agency with information and advice. The DMSB will set up telephone conferences twice a year to evaluate current safety data. Therefore, the sponsor will provide up-to-date safety data, including a summary of AEs, line listing of SAEs and adverse device effects (ADEs). In case of a high number of severe unexpected events in between DMSB meetings or a case of a Suspected Unexpected Serious Adverse Reaction (SUSAR) or other medically important conditions, the DMSB will be informed by the sponsor immediately and may give advice for further procedures if required. An interim analysis is not planned.

**Stopping rules**

(a)For patients:

Placental abruption, indication for interruption of pregnancy (e.g., HELLP syndrome, pathological CTG, fetal bradycardia, eclampsia and umbilical cord prolapse), signs of chorioamnionitis (maternal fever > 37.8 °C and two or more of the following criteria: uterine tenderness, malodorous vaginal discharge, maternal leukocytosis > 15,000 cells/mm^3^ (without corticosteroids), maternal tachycardia > 100 beats/min and fetal heart rate > 160 bpm), CRP > 20 mg/dL, increased concentrations of interleukine-6 (>7 pg/mL), positive bacteriologic examination of the amniotic fluid, pos. Gram-stained sediment or IL-6 concentration > 2600 pg/mL or WBC > 30 mm^3^.

(b)For participating centers:

Inability to recruit the patients and complications during the catheter implantation, such as placental abruption, damage of the fetus or umbilical cord, fetal bleeding or death (audit after first complication, center ex in case 2 or more complications/year).

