## 1. Introduction

Mid-trimester PPROM complicates approximately 0.4–0.7% of all pregnancies and is associated with very high neonatal mortality and severe morbidity [1,2,3,4]. The causes of the mid-trimester PPROM are multifactorial [4]. The mechanism of PPROM is discussed as altered membrane morphology, including marked swelling and disruption of the collagen network, which can be triggered by bacterial products and pro-inflammatory cytokines and involves the activation of matrix metalloproteinases [4,5,6,7].

The propagation of bacteria is an important contributing factor in adverse neonatal and maternal outcomes after PPROM [1,4,8]. Gomez et al. reported that antibiotics failed to eliminate the amniotic infection in 83% of PPROM cases [9]. The “classic PPROM” with oligo/anhydramnion is associated with a short latency period and worse neonatal outcome compared to similar gestational aged neonates [4].

In Germany, the number of pregnant women with mid-trimester classic PPROM has been calculated to be about 5 thousand–7 thousand per year. Generally, about 40% of very preterm infants who survive the initial NICU die during next 5 years of life, and the long-term morbidity of the survivors remain high. Furthermore, more than 40% of surviving neonates following PPROM prior to 25 weeks of gestation develop bronchopulmonary dysplasia (BPD) later on [4,10].

The **fetal inflammatory response syndrome (FIRS)**, a systemic inflammation determined by elevated fetal plasma IL-6 concentrations and histological signs of funisitis in the umbilical cord, is an additional independent risk factor for the occurrence of severe neonatal morbidity [11].

The lavage effect of continuous amnioinfusion could protect the fetus and amniotic cavity from bacterial colonization; reduce the inflammatory response; and thus protect the neonate from major complications, such as pulmonary hypoplasia, sepsis, cerebral palsy and joint deformities [4,12,13,14,15].

Serial amnioinfusions with standard electrolyte solutions have seen little or no effects onto neonatal outcome probably because of the immediate loss of fluid after the intervention and possible negative effect of longtime saline solution on the fetus [4,14,16,17,18,19].

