**Exclusion criteria:**

The patients with fetal death, high rupture of membranes, pre-PPROM, premature labor, placental abnormalities, placental abruption, evidence of major structural or chromosomal abnormalities, indication for termination of pregnancy (e.g., HELLP syndrome, pathological CTG (if present), fetal bradycardia, eclampsia and umbilical cord prolapse), cervical insufficiency, placenta previa, signs of chorioamnionitis (maternal fever > 37.8 °C and two or more of the following criteria: uterine tenderness, malodorous vaginal discharge, maternal leukocytosis > 15,000 cells/mm^3^ (without corticosteroids), maternal tachycardia > 100 beats/min and fetal heart rate > 160 bpm) and CRP > 20 mg/dL (C reactive protein).

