**Intervention and control groups**

**Control group**

The PPROM patients of the control group receive the standard therapy related to the German Guidelines, including antibiotic therapy (Amoxicillin/Clarithromycin therapy or 7 days Amoxicillin and once Azithromycin 1 g per oz) or other antibiotics according to recommendations of the physicians from the microbiology department based on the culture results for at least 7 days [22]. There must be a daily blood analysis (hemoglobin, leucocytes, thrombocytes, CRP and interleucine-6) and a cervical smear every 5 days. The RDS prophylaxis must be performed before randomization.

**Amnion Flush interventional group** (Figure 3)

The PPROM patients of the Amnion Flush group will receive the standard therapy related to the German Guidelines, like the control group [22]. Additionally, after the amnioinfusion of 300 mL (Amnion Flush Solution Serumwerk AG, Bernburg, Germany) through the 22G needle (Figure 4A), under local anesthesia, an ultrasound-guided perinatal catheter with an anchor system (0.65 mm Diameter, CE 0481, PakuMed GmbH, Essen, Germany) will be inserted into the amniotic cavity through the 18G needle for the continuous amnioinfusion with 100 mL/h of Amnion Flush Solution, (Serumwerk Bernburg AG, Germany) until delivery (latest on beginning of 34/0 weeks of gestation) [4,12,13] (Figure 4B,C).

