**flush-out group subjects**										
**catheter implantation/change**		**x**			**x**					
**amnion flush**		**x**	**x**							
**microbiology (amniotic fluid)**				**x**	**x**					

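### The patient stopping rules do not fit the entry criteria (IL-6) or the sampling schedule (amniotic fluid), so a woman can enter already meeting a stop and the flush arm has an extra route to stopping

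*Protocol article*

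**What the plan says.** **Stopping rules, (a) For patients.** One list covers all patients and names no arm. It contains the clinical signs of chorioamnionitis, CRP above 20 mg/dL, "increased concentrations of interleukine-6 (>7 pg/mL" and then "positive bacteriologic examination of the amniotic fluid, pos. Gram-stained sediment or IL-6 concentration > 2600 pg/mL" or a white-cell count above 30. No specimen is named for the 7 pg/mL limit. The section does not say what stopping ends.

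**Exclusion criteria.** These repeat the clinical definition, "signs of chorioamnionitis (maternal fever > 37.8 °C and two or more of the following criteria", and the same CRP limit. They set no IL-6 limit and no amniotic-fluid limit.

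**Intervention and control groups.** Controls have a "daily blood analysis (hemoglobin, leucocytes, thrombocytes, CRP and interleucine-6" and "a cervical smear every 5 days". The flush arm receives the same standard therapy plus the infusion, which runs until delivery or at latest 34/0 weeks.

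**Table 1.** The row "microbiology (amniotic fluid" is marked every 7 days and as needed, and it stands only in the block for "flush-out group subjects". The block for all subjects has no amniotic-fluid row. It shows blood and biochemistry at screening, at randomisation and daily. Catheter implantation is marked at randomisation, day 0.

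**The concern.** A stopping list applied after randomisation should agree with the entry list and with what is measured in each arm. Here it does neither in full.

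On entry, a woman whose IL-6 is above 7 pg/mL is eligible as written and meets a stopping rule from the start. In the flush arm she may undergo two punctures and catheter placement for a treatment that the rules then end. She carries the procedural risk and contributes little treatment contrast.

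On sampling, the flush arm is tested on schedule for four amniotic-fluid criteria for which controls are not. A finding of this kind can end treatment early in that arm. The sample size assumes that the intervention prolongs gestation by about two weeks, so early ends to the infusion work directly against the effect the trial is sized to detect.

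**Working it through.** **Step 1. Set the lists side by side.**

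| Criterion | Exclusion | Stopping | Scheduled test, control | Scheduled test, flush |
|---|---|---|---|---|
| Clinical signs of chorioamnionitis | yes | yes | no arm named | no arm named |
| CRP > 20 mg/dL | yes | yes | daily blood | daily blood |
| IL-6 > 7 pg/mL (specimen not named) | no | yes | daily blood | daily blood |
| Amniotic-fluid culture, Gram stain, IL-6 > 2600 pg/mL, WBC > 30 | no | yes | none | amniotic-fluid microbiology every 7 days and as needed |

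The daily panel is stated for controls and carried to the flush arm because that arm is treated like the control group. That the 7 pg/mL limit refers to maternal blood is inferred from this panel.

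Row 3 is the entry/stopping mismatch, and it is the same in both arms. Row 4 is the arm difference.

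**Step 2. Reproduce the planned size.** Inputs from Sample size and Statistic: monthly hazards 0.0851 (control) and 0.035 (intervention), loss hazard 0.0088, 21 months of accrual, one year of follow-up, two-sided 5%, power 80%, 34 per group.

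- HR = 0.035 / 0.0851 = 0.411; ln HR = −0.888; (1.960 + 0.842)² = 7.849.
- Events, Schoenfeld: 4 × 7.849 / 0.888² = 39.8, so 40.
- Events, Freedman: 7.849 × (1.411 / 0.589)² = 45.1, so 46.
- Event probability per arm, with s = h + 0.0088: (h/s) × [1 − (e^(−12s) − e^(−33s)) / (21s)]. This gives 0.778 (control) and 0.490 (flush), mean 0.634.
- Per arm, using unrounded events: 39.8 / 0.634 / 2 gives 32; 45.1 / 0.634 / 2 gives 36.

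The stated 34 lies between the two, so the planned figure is reproduced. This takes follow-up to run to a common date 12 months after the last entry. With follow-up cut at 12 months for each woman, the same formulas give 43 and 49 per arm, which is a separate matter.

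**Step 3. Illustrate dilution on the same basis.** Assume that a share q of the flush arm stops so early that these women have the control hazard. One-year event-free survival is then S = (1 − q) × 0.657 + q × 0.360. The effective hazard is −ln(S)/12, and the HR is that hazard divided by 0.0851. Expected events D = 34 × (sum of the two event probabilities). Power is Φ(√D × |ln HR| / 2 − 1.96) by Schoenfeld and Φ(√D × (1 − HR)/(1 + HR) − 1.96) by Freedman.

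| q | S | HR | D | Power, Freedman to Schoenfeld |
|---|---|---|---|---|
| 0 | 0.657 | 0.411 | 43.1 | 78–83% |
| 10% (about 3 of 34) | 0.627 | 0.457 | 44.3 | 70–74% |
| 20% (about 7 of 34) | 0.598 | 0.504 | 45.4 | 60–64% |
| 30% (about 10 of 34) | 0.568 | 0.554 | 46.5 | 50–52% |

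The document gives no value for q. The table shows only how sensitive the design is if such stops occur.

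**The case against.** Much can be said for the plan, and most of it limits the point without removing it.

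- **IL-6 is not an arm asymmetry.** It is in the daily panel of both arms, and its level at entry is balanced in expectation by randomisation. A reader might infer that this criterion tilts the comparison. The text does not support that. Nor does Table 1 name IL-6 among the screening tests, so a result need not be known before randomisation. A rule after entry may also be stricter than the entry rule. What stands is that nothing as written prevents randomising a woman who already meets a stop.
- **Controls are not immune from stopping.** A reader might infer that an infected control can never be stopped. She can be, on clinical signs, CRP or IL-6. The Discussion also mentions amniotic-fluid examination as general monitoring with no arm named, and a schedule does not forbid an unscheduled sample. What stands is that only the flush arm is scheduled for these tests.
- **Some of the difference comes with the intervention.** Controls have little or no fluid and no catheter, and if stopping means ending the infusion, they have nothing to end. A safety stop in one arm is part of that arm's treatment policy. It can dilute an as-randomised comparison but does not bias it. This stands.
- **No stopping rate can be derived.** The Introduction cites a study that "reported that antibiotics failed to eliminate the amniotic infection in 83% of PPROM cases". It is tempting to combine this with an assumed prevalence of infection. The document gives no prevalence, and the figure concerns antibiotics, whereas the trial's rationale is that lavage clears bacteria.
- **Loss to follow-up is not shown.** A reader might suppose that stopped women leave the trial. The text does not say so, and Table 1 schedules assessment to day 365 with no exception for them.

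**Conclusion.** The point holds in a limited form, as a conflict between stated rules that should be resolved. The entry and stopping lists disagree on IL-6 in both arms alike. This can expose a woman to catheter placement when a stopping rule is already met, and it can dilute the effect. Separately, the amniotic-fluid criteria are scheduled for testing only in the flush arm, so that arm has one more route by which treatment can end early.

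The consequence is possible loss of power. It is not bias in an as-randomised comparison. Its size is unknown. The fall to 70–74%, 60–64% or 50–52% rests on assumed early-stopping shares of 10%, 20% and 30%, on stopped women having the full control hazard, and on the planned log-rank design. If they keep part of the benefit, the loss is smaller.

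**What to change.** Reconcile Stopping rules (a), Exclusion criteria, Intervention and control groups, and Table 1:

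1. For each stopping criterion, name the specimen and the arm or arms to which it applies, and make Table 1 agree.
2. Align the entry and stopping lists so that no woman can be randomised while already meeting a stopping criterion. How to do this, and at what thresholds, is a clinical choice for the sponsor.
3. State in the stopping rules what stopping ends in each arm: the infusion, the pregnancy or participation.

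The cost is a protocol clarification. Items 1 and 3 need no new procedure and no change to the sample size. Item 2 may affect who is eligible, depending on the sponsor's choice.
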